For “negative” emotions from posts for “diurnal activity,” we will be applying the text2emotion Python function to extract the emotional words used on the posts. However, the text2emotion library shows 5 different emotions, namely happy, sad, angry, surprise, and fear. However, here, we will be dealing with the negative feelings from Facebook posts.

First, our main purpose is to clean the data to make them appropriate for analyzing emotions. For the data cleaning process, we need to follow several steps. For instance, we need to remove the unwanted texts or words from the posts (ie, the words that have low frequency based on term frequency–inverse document frequency), apply various tools of the Natural Language Toolkit for sentiment analysis, and extract the better-preprocessed posts from the previous preprocessed posts. Second, we need to figure out the emotional words from the preprocessed texts and then use them for further visualization of the emotions. Finally, we need to observe the scores of the emotions. The higher the score from 1 of the 5 categories, the more the emotion will belong to that group.

After that, we intend to observe the emojis from the posts to investigate what type of nonverbal attributes a person who is depressed has both during the daytime and nighttime while writing posts on SM. This will help us figure out which emojis a person who is depressed uses repeatedly during the night. Several studies were conducted on emojis [89-92], indicating how they coincide with the linguistic style of a person. For instance, the emojis that are inclined with the negative words from LIWC are “anger,” “money,” “ingest,” “family,” “home,” and “death” [89].

As mentioned earlier, we will be focusing on the sentiments in the posts and the frequently used emojis by an individual during nighttime. Moreover, we will be considering how the emotions in a person’s post and the number of emojis used on a post are correlated with diurnal activity. For that, we will be using the formula for MI, as it consists of both joint probability and marginal probability. “Joint probability” will help investigate the relationship between the emotions in the posts and the number of emojis used, applying a condition, that is, if we work on the sentiments in the posts, then the number of emojis will be kept constant, and vice versa. In contrast, “marginal probability” will help us extract 1 feature at a time (ie, the features will be independent of one another).

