There will be a change in the formula for both *“*diurnal activity*”* and MI (ie, in the *“*diurnal activity” formula, the number of posts will be denoted as “Po,” and not XG). For MI, instead of “X” and “Y,” we will write “Po” and “E,” respectively. Here, “Po” will indicate the posts written by an individual during nighttime, and “E” will indicate the types of emojis used by that individual.

The modified formulas for diurnal activity and MI are as follows:

(Po(d,h)) / (∑Po(d,i)) **(3)**

MI(Po,E) = ∑∑P(Po,E)e log (P(Po,E)e) / (P(Po)e × P(E)e) **(4)**

To find out the MI, we will consider various combinations for the number of “negative” posts and emojis used by an individual. We will consider the values of both Po and E as binary 1 (ie, Po=1 and E=1) if the posts are “negative” and the emojis are used.

In contrast, we will consider the values of both Po and E as binary 0 (ie, Po=0 and E=0) if the posts are “nonnegative” and no emojis are used in the post.

There are other combinations as well, that is, Po=0 and E=1 if the number of posts is “nonnegative” and emojis are applied in the posts, and Po=1 and E=0 if the posts are “negative” and no emojis are used in the posts.

Here, we will eliminate Po=0 and E=1 and Po=0 and E=0, as we will not deal with “nonnegative” posts (ie, Po=0) and “zero emojis” (ie, E=0).

The highest value of MI will indicate both the number of “negative” posts and “emojis” (Po=1 and E=1) used. In contrast, the lowest value will indicate either the number of “nonnegative” posts and “emojis” (Po=0 and E=1) used or the number of “nonnegative” posts and “zero emojis” (Po=0 and E=0).

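### Formula (4) defines E as emoji type but scores it as any emoji versus none, so its mutual information cannot show which emojis go with negative posts

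*Protocol article*

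**What the plan says.** All the relevant text is under Methods, Text and Behavior Analysis, Diurnal Activity.

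- **Aim.** Looking at emojis in day and night posts is meant to show "which emojis a person who is depressed uses repeatedly during the night". The Results section repeats the interest in emoji types that recur.
- **Reason for using MI.** The authors consider how post emotion and "the number of emojis used on a post are correlated with diurnal activity. For that, we will be using the formula for MI". The joint probability is said to address "the relationship between the emotions in the posts and the number of emojis used". Here the emoji quantity is a count.
- **Definition at formula (4).** "E” will indicate the types of emojis used by that individual". Here it is a type.
- **Scoring rule.** Po and E are both taken "as binary 1 (ie, Po=1 and E=1) if the posts are “negative” and the emojis are used". The opposite cell is "ie, Po=0 and E=0) if the posts are “nonnegative” and no emojis are used in the post". Here E is any emoji, yes or no, and the text restates E=0 as the absence of any emoji.
- **Cells kept.** Both combinations with Po=0 are then eliminated.

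The subscript e appears on every probability in formulas (2) and (4) but is not defined for either.

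**The concern.** The definition and the scoring rule for E disagree, and only the scoring rule can be executed. It puts every emoji into one category, so formula (4) measures at most whether negative posts contain emojis more or less often than other posts. It does not measure whether particular emojis mark negative posts, which is what the definition of E points to.

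An analyst who follows the rule would get a number that looks like evidence on emoji types and is not. Two data sets with opposite type preferences would give the same value.

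**Working it through.** The protocol states no MI value and no emoji frequencies, so there is no figure to reproduce. All inputs below are assumptions, chosen to show how the coding behaves. Logarithms are natural, so results are in nats.

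**Formula.** MI = Σ p(x,y) log[ p(x,y) / (p(x) p(y)) ], summed over the four cells of a 2×2 table (formula (4) with all posts kept).

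**Step 1: is the yes/no rule blind to type?** Take 100 negative and 100 nonnegative posts, each with no emoji, a sad one or a joy one (counts in that order).

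| Data set | Negative | Nonnegative | Yes/no MI | Sad-emoji MI | Joy-emoji MI |
|---|---|---|---|---|---|
| A | 40/55/5 | 60/5/35 | 0.0201 | 0.1675 | 0.0774 |
| B (types swapped) | 40/5/55 | 60/35/5 | 0.0201 | 0.0774 | 0.1675 |
| C (no type preference) | 40/30/30 | 60/20/20 | 0.0201 | 0.0067 | 0.0067 |

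The yes/no table is the same in all three: 60 of 100 negative and 40 of 100 nonnegative posts have an emoji. MI is therefore 0.0201 each time, although A and B have opposite preferences and C has none. The indicator per emoji separates them.

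**Step 2: how far apart can the two codings be?** Assume 30% negative posts. Among emoji-bearing posts, 80% of negative and 10% of other posts contain a sad emoji. Vary the share of posts with any emoji.

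*Emojis in 40% of both kinds.* Yes/no cells: 0.12, 0.18, 0.28, 0.42. Each equals the product of its margins (0.30 × 0.40 = 0.12, and so on), so MI = 0.000. Sad-emoji cells: 0.30 × 0.40 × 0.80 = 0.096; 0.30 − 0.096 = 0.204; 0.70 × 0.40 × 0.10 = 0.028; 0.70 − 0.028 = 0.672. The sad-emoji margin is 0.096 + 0.028 = 0.124. The four terms are 0.0910, −0.0517, −0.0317 and 0.0615, so MI = 0.069. The maximum with 30% negative posts is −0.3 log 0.3 − 0.7 log 0.7 = 0.611.

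*Other emoji rates, same method:*

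| Emojis in negative / other posts | Yes/no MI | Sad-emoji MI |
|---|---|---|
| 40% / 40% | 0.000 | 0.069 |
| 40% / 20% | 0.021 | 0.090 |
| 20% / 40% | 0.020 | 0.019 |

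*Weaker inputs at equal emoji rates.* With a 50%/20% sad split and emojis in 40% of posts, the result is 0.000 against 0.014. With the 80%/10% split and emojis in 20% of posts, it is 0.000 against 0.032.

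In the last row of the table the two values agree in size but not in meaning. Negative posts have fewer emojis (20% against 40%) yet more sad ones (0.20 × 0.80 = 16% against 0.40 × 0.10 = 4%). MI has no sign, so the yes/no value reveals neither fact about type.

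**Step 3: the eliminated cells.** With the Po=0 posts removed, P(Po=1) = 1 and P(Po=1, E) = P(E). Every logarithm is log 1 = 0, so MI = 0 under any coding of E. Recoding E alone therefore changes no result; the nonnegative posts must be kept as well.

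**The case against.** Five points can be made for the plan.

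1. **Emoji types may be found another way.** The wording about which emojis recur speaks of observing and examining them, and MI is introduced afterwards for a further question. A reader might infer that the study cannot identify common emojis at all. The document does not support that, because a frequency tally remains open. Formula (4) is still said to use type and does not.

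2. **The subscript e could mean each emoji.** This is possible, and the fault would then be loose prose. But e is never defined, and E=0 is described as no emoji in the post, not as one emoji being absent. Nor can formula (2) be cited as already working per emoji: its x is also coded as applying emojis or not.

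3. **The zero is a product of the assumptions.** This stands. Yes/no MI is 0.000 only when emoji use is equal in both kinds of post. A reader might infer that a real difference in type would be reported as no association. That goes too far: the gap between codings varies and can vanish, and the document states no rule for declaring an association absent.

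4. **The count wording is not a rival definition.** It comes before the symbol E is introduced, so it is better read as loose description than as another formal meaning of E.

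5. **The prediction model is not shown to depend on it.** Textbox 1 lists a diurnal activity value but no MI, and emoji counts are a separate feature in the overview of Text and Behavior Analysis. The section on previous work names emoji use, not formula (4), as a distinctive parameter. Harm to model performance cannot be inferred.

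**Conclusion.** The point holds in a limited form. The definition of E at formula (4) conflicts with the scoring rule beside it, and under that rule the statistic contains no information on emoji type. This follows from the coding alone and needs no assumption about frequencies.

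The size of the loss does depend on assumptions. Across the three emoji-rate scenarios with the 80%/10% split, the per-emoji value exceeds the yes/no value by 0.069 − 0.000 = 0.069 nats in the first and 0.090 − 0.021 = 0.069 nats in the second. In the third they are about equal (0.020 and 0.019). These figures presuppose that nonnegative posts are kept, which the current text does not do.

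The consequence is confined to a descriptive emoji analysis. It is worth correcting because the present rule defeats its own definition and the remedy is nearly free.

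**What to change.** In the Diurnal Activity section:

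- Replace the coding of E with one indicator per emoji: E_e = 1 if emoji e appears in the post, 0 otherwise.
- State that the subscript e in formula (4) denotes the emoji.
- Compute MI separately for each frequent emoji, over all posts, negative and nonnegative, and delete the sentence that eliminates the Po=0 combinations.
- Report next to each MI the proportion of negative and of nonnegative posts that contain the emoji, since MI shows no direction.
- Keep the number of emojis as the separate count feature already listed in the overview of Text and Behavior Analysis, and remove the count wording from the description of MI.

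The cost is a few sentences and one MI per frequent emoji. No additional data are needed.

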#### Advertisement Analysis

Participants revealed a tendency to reduce their SM posts during periods of low moods, with the belief that their SM content might not accurately depict their depressive state. SM platforms such as Facebook use algorithms to direct advertisements to suitable users, leveraging search keywords and previously accessed links. A subset of participants acknowledged the practice of targeted advertising, while a minority reported posting specifically to seek support. In addition, participants acknowledged the existing use of targeted advertising and expressed a preference for its application in mental health care provisioning as opposed to its current use. Individuals experiencing depression tend to conduct searches related to health-related topics, resulting in personalized advertisements that align with their search preferences.

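### The per-person mutual information in formula (4) depends on how many posts a person has, so its size cannot be read as association between negative posts and emojis

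*Protocol article*

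**What the plan says.** All of this is in the protocol article, Methods, Diurnal Activity. Po "will indicate the posts written by an individual during nighttime", and E "will indicate the types of emojis used by that individual". The formula is "MI(Po,E) = ∑∑P(Po,E)e log (P(Po,E)e) / (P(Po)e × P(E)e"). Both variables are then coded 0/1 ("We will consider the values of both Po and E as binary 1" when a post is negative and carries emojis), and the four combinations are listed under the statement "To find out the MI, we will consider various combinations for the number of" negative posts and emojis used by an individual.

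Two further statements bear on the result. First, the nonnegative-post combinations are to be removed: "Here, we will eliminate Po=0 and E=1 and Po=0 and E=0, as we will not deal with" nonnegative posts and zero emojis. Second, the size of MI is given a meaning: "The highest value of MI will indicate both the number of" negative posts and emojis, while the lowest value is said to indicate one of the two Po=0 combinations, although these have just been removed.

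The section names no estimator for the probabilities.

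On posting volume, the Advertisement Analysis section says: "Participants revealed a tendency to reduce their SM posts during periods of low moods". The SM Engagement Analysis section says that people with clinical depression spend more time on social media than others. Diurnal Activity itself says that depressed individuals are most active at night.

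**The concern.** MI estimated by putting observed proportions into the formula cannot be negative. Chance imbalance in a small table therefore always pushes it up, and the push shrinks as posts accumulate. Two people with the same (absent) relation between negative content and emoji use will get different expected values because one has 20 nighttime posts and the other 200. Restricting to nighttime posts makes each person's table smaller still.

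The article gives meaning to high and low values. If these values are compared between people, or passed to a model, part of what is read as emotional expression is posting volume. If posting volume differs by depression status, MI can appear to separate the groups with no association in anyone.

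**Working it through.** **Inputs.** From the article: one table per individual, two binary variables, formula (4), and the removal of the Po=0 combinations. Not in the article, so assumed: posts per person (1 to 1000), shares of negative posts (p) and of posts with an emoji (q) between 0.05 and 0.5, natural logarithms, and probabilities taken as the person's own proportions. The article states no MI value, so there is no figure to reproduce.

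**Step 1: expected MI with no association, full table.** The first-order result is (r-1)(c-1)/(2N), which for two-by-two is 1/(2N). Values at p = q = 0.3 (exact enumeration to N=100, simulation at N=1000):

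| N posts | 1/(2N) | Expected MI |
|---|---|---|
| 10 | 0.050 | 0.063 |
| 20 | 0.025 | 0.030 |
| 50 | 0.010 | 0.0106 |
| 100 | 0.005 | 0.0051 |
| 1000 | 0.0005 | 0.0005 |

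The approximation fails for very few posts or rare margins. At N=1, MI is always 0. At p=0.05, q=0.10 the expected value is 0.0135 at N=5 (rule: 0.100) and 0.0118 at N=20 (rule: 0.025). If E were K emoji types instead of yes/no, the rule becomes (K-1)/(2N). For K=5 and N=20 that is 4/40 = 0.100, and simulation gives 0.124.

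**Step 2: compare with a real association.** With both margins held at 0.3, an odds ratio of 2 gives true MI 0.011 and an odds ratio of 3 gives 0.028. Noise at 20 posts (0.030) is as large as the latter. With no association in either, a 20-post person scores above a 200-post person 82% of the time.

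**Step 3: apply the elimination.** It can be read in three ways:

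- Drop only the two Po=0 terms from the double sum. The remainder is still non-negative, and its null mean is about (1-p)/(2N). At p=0.3, N=20 that is 0.7/40 = 0.0175 to first order; by simulation it is about 0.022.
- Delete the nonnegative posts from the data. Po is then constant, and MI is exactly 0 for everyone.
- Keep only the Po=1, E=1 term. Its null mean at N=20 is 0.0155, and it can be negative for an individual.

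**Step 4: separation from volume alone.** No association in anyone, log-normal post counts with log-SD 0.8. AUC for the lower-volume group scoring higher:

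| Version and margins (p/q) | Medians 50 v 100 | Medians 25 v 100 |
|---|---|---|
| Full table, 0.3/0.3 | 0.60 | 0.68 |
| Po=0 terms dropped, 0.3/0.3 | 0.60 | 0.68 |
| (1,1) term only, 0.3/0.3 | 0.51 | 0.54 |
| Full table, 0.05/0.10 | about 0.53 | 0.46 |

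At equal volume the AUC is 0.50. If the other group has the lower volume, 0.60 and 0.68 become 0.40 and 0.32.

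**The case against.** **The plan removes the Po=0 cells, so the full-table bias does not apply.** This stands only in part. The bias disappears if the posts are deleted, but then the feature is zero for everyone. It has little effect on separation if only the (1,1) term is kept. On the most literal reading, where two terms leave the sum, it remains with the same AUCs. The article also still interprets the removed cells, so it cannot be said which version will be computed.

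**Depressed users would score higher because they post less.** A reader might infer this from the Advertisement Analysis sentence. The article does not support it. SM Engagement Analysis and Diurnal Activity point to more activity, especially at night, and Po is nighttime posts. Only a volume difference of unknown direction can be claimed. At rare margins, low posters can even score lower.

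**The final model's performance would be spurious.** This does not follow either. MI is not named in Textbox 1 or under ML Modeling, so its use as a classifier input is only implied. The highest and lowest sentences contrast cell combinations and do not explicitly rank people. The Overview of Text and Behavior Analysis already lists number of posts and posting frequency. In the Step 4 scenario, post count alone gives AUC 0.73 and 0.89, above MI's 0.60 and 0.68. The harm is to the interpretation of this one measure; the effect on the final model is unquantified.

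**Estimator details belong in a fuller plan.** It is fair that the absence of a stated correction or minimum count is not in itself a fault of an article. But the article chose the statistic, wrote the formula, coded the variables and said how values are read, and that stated reading is what fails.

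**Conclusion.** The point holds in limited form. If formula (4) is filled with a person's own post proportions, its value is confounded with that person's number of nighttime posts, in a direction the article leaves open. The null mean is about 1/(2N) for the full table or (1-p)/(2N) with the Po=0 terms dropped. At 30%/30% margins and tens of posts this is as large as a real odds ratio of 2 to 3, and a two- to fourfold difference in median volume gives AUC 0.60 to 0.68 with no association. With rare negative posts and emojis (5%/10%) the effect is small or reversed. Margins, post counts and the plug-in estimator are assumptions. It is a worthwhile, inexpensive correction to one stated measure and does not invalidate the prediction model.

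**What to change.** In Diurnal Activity:

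1. Reconcile the elimination sentence with the sentences that interpret the Po=0 combinations, and keep all four cells in formula (4). Restoring the cells alone would leave the volume dependence in place.
2. Replace plug-in MI by a volume-corrected measure. One option is MI minus its mean over permutations of the emoji indicator within the person. The other is the log odds ratio with 0.5 added to each cell, which also shows direction: MI cannot tell whether emojis go with negative or with nonnegative posts.
3. State a minimum number of nighttime posts for computing the measure.
4. Interpret it alongside the post count already listed among the behaviors.

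The cost is a few lines of code and a sentence or two of text. The measure will be missing for people below the minimum.

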#### Diurnal Activity

Diurnal activity indicates the activeness of a person on SM both during the daytime and at night. It has been mentioned that individuals who are depressed are most active during the night [6,30,86]. In our study, we will investigate the moods [87] of all people who have written posts on SM. We intend to determine the emotions of a person who is depressed (ie, to visualize whether the person is actually depressed).

Diurnal activity will be calculated using the following formula:

XG(d,h) / ∑XG(d,i) **(1)**

where XG (d,h) indicates the average timing of the total number of posts made in hours (h) and days (d), the G in XG indicates the country where the post was made. In addition, h indicates a value from 0 to 23 (ie, an average number of posts is considered up to 11 PM).

Another study indicates a positive relationship between the use of emojis and genders (ie, women use more emojis than men), and the most frequently used emoji was the emoji representing tears of joy, with a use percentage of 22.2% and 18.9% among women and men, respectively. However, to investigate the emoji choices of both genders, a statistical analysis was carried out, named “mutual Information” (MI), which calculates the use of emojis by both men and women [88]:

MI(X;Y)e = ∑∑P(x,y)e log (P(x,y)e) / (P(x)e × P(y)e) **(2)**

where X indicates whether the gender (either men or women) uses an emoji. Here, the value of x will be equal to 1 if a user applies emojis, and if the value of x is equal to 0, then the user does not apply emojis. However, Y indicates a user’s gender (ie, for men, the value of y will be equal to 1; for women, the value of y will be equal to 1). Here, X is represented as a member of x, and Y is represented as a member of y. In contrast, p(x,y)e indicates the joint probability of X and Y, whereas p(x)e and p(y)e indicate the marginal probability of X and Y [88].

For analyzing the data from Facebook, we will observe the time stamps for negative posts and the types of emojis that are used frequently on posts related depression. We will be focusing on the formulas given earlier, but we will adjust the variables to suit our needs.

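### Removing the nonnegative posts leaves the emoji mutual information with nothing to measure, and its stated high/low reading is wrong even on the full table

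*Protocol article*

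**What the plan says.** All of this is in the protocol article, Diurnal Activity, around the modified formulas (3) and (4).

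- **Formula.** MI is taken over Po and E from joint and marginal probabilities: "In contrast, p(x,y)e indicates the joint probability of X and Y, whereas p(x)e and p(y)e indicate the marginal probability of X and Y". Formula (4) substitutes Po and E for X and Y.
- **Coding.** "We will consider the values of both Po and E as binary 1" when the post is negative and an emoji is used. Po=0 is a nonnegative post and E=0 is no emoji. The combinations refer to "posts and emojis used by an individual", so the calculation is per person.
- **Elimination.** "Here, we will eliminate Po=0 and E=1 and Po=0 and E=0, as we will not deal with" nonnegative posts. The same sentence also gives zero emojis (E=0) as something not dealt with, although it does not name the Po=1, E=0 combination among those removed.
- **Interpretation.** "The highest value of MI will indicate both the number of" negative posts and emojis (Po=1, E=1). The lowest value is said to indicate nonnegative posts, with or without emojis.
- **Another definition of Po.** Just before formulas (3) and (4), Po "will indicate the posts written by an individual during nighttime", and E denotes the types of emojis rather than whether any was used.

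**The concern.** MI compares a joint distribution with the product of its marginals. It needs both variables to vary. A rule that keeps only one level of Po takes away the contrast on which the measure rests, so a feature meant to link mood and emoji use would be the same number for everyone who has one.

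The interpretation is a separate problem. MI measures how strongly two variables depend on each other. It does not say which cell is common or in which direction the dependence runs. Someone following the article's reading could take a high score as a sign of negative posts with emojis when the data show the opposite pattern. The reading also assigns the low end of the scale to combinations that the elimination sentence has just removed.

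**Working it through.** The article gives no MI value to reproduce. The check is algebraic, with illustrative post counts that are assumptions and not taken from the document. Formula (4) is read as standard discrete MI with natural logs:

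MI = Σ Σ P(Po,E) · ln[ P(Po,E) / (P(Po) · P(E)) ].

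**1. After the Po=0 posts are removed.** P(Po=1) = 1 and P(1,E) = P(E). Each term is P(E) · ln[P(E) / (1 · P(E))] = P(E) · ln 1 = 0. This holds for any log base and for emoji types as well as a yes/no emoji code. In 100,000 random tables with binary E the largest |MI| was 0; in 20,000 tables with 10 emoji types it was 2.8e-16, which is rounding. If E=0 is dropped too, one cell remains and MI = 1 · ln(1/(1 · 1)) = 0. A participant with no negative posts has 0/0, so the feature is undefined.

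**2. The full table.** Take 800 posts: nonnegative, 350 without and 150 with emoji; negative, 100 without and 200 with. The marginals are P(Po=0) = 0.625, P(Po=1) = 0.375, P(E=0) = 0.5625, P(E=1) = 0.4375.

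- Po=0, E=0: 0.4375 · ln(0.4375/0.3516) = 0.0957
- Po=0, E=1: 0.1875 · ln(0.1875/0.2734) = -0.0707
- Po=1, E=0: 0.125 · ln(0.125/0.2109) = -0.0654
- Po=1, E=1: 0.25 · ln(0.25/0.1641) = 0.1053

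The sum is 0.0648 nats. Swapping the emoji columns (nonnegative 150 without and 350 with; negative 200 without and 100 with) gives the same four terms in other cells, so MI is again 0.0648. With the Po=0 row removed, both tables give 0.

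**3. The stated high/low reading.** Counts are in the order negative with emoji, negative without, nonnegative with, nonnegative without.

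- 100/0/0/0: MI = 0, the minimum, where the article expects the highest value.
- 0/50/50/0: MI = ln 2 = 0.693, the binary maximum, although no negative post carries an emoji.
- 50/0/0/50: also 0.693.
- 81/9/9/1: MI = 0, although 81 of 100 posts are negative with emojis.

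**4. Dropping terms only.** Suppose the Po=0 terms are left out but the probabilities still come from all posts. In the 800-post example the two Po=1 terms sum to 0.1053 - 0.0654 = 0.0399, and the mirror table gives the same. In random tables this partial sum ran from 0 to about 0.34. If only the (1,1) term is kept, the example gives +0.105 and its mirror -0.065. These quantities vary, but neither is MI.

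**The case against.** The best defence is that the article eliminates combinations and never says that probabilities are recalculated on the remaining posts. Its next lines still place Po=0 combinations at the low end, which suggests they stay in the probability base. On that reading the feature is not constant, and the (1,1) term alone would even carry direction. This stands as an ambiguity, so a reader should not infer that the feature is zero whatever the authors meant. It does not rescue the text: the reason given is that nonnegative posts will not be dealt with, formula (4) still prints a double sum, and no partial sum is described.

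Three stronger inferences are tempting and not supported.

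- **That formula (3) loses the night-versus-day contrast.** The night-time definition follows the sentence on MI and may apply only there. For formula (3) the article announces a change of notation, and its source formula runs over hours 0 to 23. Shares that sum to 1 are no defect, since they do so over 24 hours as well. What stands is that Po has two definitions.
- **That the remark on joint probability, "if we work on the sentiments in the posts, then the number of emojis will be kept constant, and vice versa", by itself forces MI to zero.** It can be a loose description of looking at one variable at a time.
- **That the prediction model as a whole is undermined.** Emoji counts enter separately in the Overview of Text and Behavior Analysis, and Textbox 1 lists the diurnal activity value but does not name MI.

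**Conclusion.** The point holds, at moderate severity. On the natural reading, the elimination rule makes the MI feature exactly 0 for every participant with at least one negative post and undefined for the others, so it carries no information. On the alternative reading, the computed quantity is not mutual information.

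The error of interpretation does not depend on that choice. For true MI on the full table, mirror-image patterns score the same (0.065 nats in the example), and a person whose posts are all negative with emojis scores 0.

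This rests on reading formula (4) as standard MI and on the negative/nonnegative coding that the elimination sentence itself uses. A constant feature would be uninformative, not biasing.

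**What to change.** 1. Delete the elimination sentence and compute MI per participant on the full 2x2 table of negative/nonnegative by emoji/no emoji.
2. Remove the highest/lowest interpretation and report a directional measure beside MI. One option is the log odds ratio with 0.5 added to each cell. For the 800-post example it is ln[(200.5 · 350.5)/(100.5 · 150.5)] = +1.54, and -1.54 for the mirror table. Another is to compare P(E=1|Po=1) with P(E=1|Po=0): 200/300 = 0.67 against 150/500 = 0.30 in the example, and 100/300 = 0.33 against 350/500 = 0.70 in the mirror. Either would serve.
3. Give Po one definition and use a separate symbol for night-time posting. Say likewise whether E is any emoji or the emoji type.
4. State that formula (3) uses posts from all 24 hours.

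The cost is a few sentences and a few lines of code. The posts come from the Facebook files that participants upload, so no new data are needed.
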